### Statistical Analysis

All analyses will follow the intention-to-treat principle, whereby all randomized participants will be analyzed according to their assigned study group regardless of intervention uptake, regimen changes, or follow-up completeness. Baseline characteristics will be summarized by study group using appropriate descriptive statistics.

The primary analysis will assess between-group differences in optimal PrEP adherence over time. As the primary outcome is binary and repeatedly measured, generalized linear mixed-effects logistic regression models will be used, including fixed effects for study group, time, and the group-by-time interaction and a participant-level random intercept to account for within-participant correlation. Prespecified baseline covariates will be included to improve precision and adjust for residual imbalance. Effect estimates will be presented as odds ratios with 95% CIs.

Adherence outcomes will be constructed according to the prespecified regimen-specific definitions described above. For daily PrEP users, days without a recorded PLP Camp check-in during each monitoring period will be operationally treated as days without reported pill intake based on previous literature [36,37]. For event-driven PrEP users, adherence will be assessed only for reported sexual encounters according to the standard 2-1-1 regimen; intervals without a submitted PLP Camp check-in will be treated as intervals without a reported sexual encounter.

Secondary outcomes will be analyzed using mixed-effects models appropriate to outcome type, with fixed effects for study group, time, and the group-by-time interaction and participant-level random effects. All tests will be 2 sided, with statistical significance defined as *P*<.05. Analyses will be conducted using the R software.

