**Methods:**

The Real-Time Monitoring and Precision Intervention for HIV PrEP Adherence (REMOTE) trial is a parallel-group, open-label, online-delivered, active-controlled, and stratified randomized controlled trial conducted among 430 e-consumers of PrEP (320 event-driven regimen users and 110 daily regimen users) in China. People who have purchased PrEP online, have taken PrEP in the previous 3 months, and plan to continue for the next 6 months will be stratified by regimen type and randomized into control and intervention groups at a 1:1 ratio. A WeChat-based digital platform will deliver the REMOTE intervention. The monitoring module follows ecological momentary assessment principles. The intervention design is guided by the stages of change theory, tailoring strategies to different nonadherence risks based on monitoring results. Intervention components include low-risk (health education and an artificial intelligence chatbot), medium-risk (peer forum and admonitory education), and high-risk (customized reminders and physician counseling) strategies. The control group will use a simplified platform with only real-time monitoring. The primary outcome is the proportion of participants achieving optimal adherence for 6 months, assessed via real-time monitoring and validated via surveys at baseline and the 1-, 3-, and 6-month follow-ups. Secondary outcomes include PrEP adherence knowledge, self-efficacy, risk perception, adherence barriers, stigma, and social support, measured via surveys. Intention-to-treat analysis will be conducted.

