### Outcomes

The primary outcome of this study is optimal PrEP adherence over the 6-month study period, defined as a binary outcome (optimal vs suboptimal adherence) and assessed separately for event-driven and daily PrEP users. Adherence will be measured primarily using EMA data collected through the PLP Camp platform version 2.0, whereas survey data collected at baseline and follow-up visits will be used to support interpretation and cross-validation of adherence-related measures.

For daily PrEP users, each PLP Camp check-in will record whether the participant has taken 1 PrEP pill within the preceding 24 hours. Adherence will be calculated as the proportion of days with reported pill intake out of all days under observation during each monitoring period. In constructing this outcome, days without a submitted PLP Camp check-in will be operationally treated as days without reported pill intake. Daily users with adherence of 80% or higher during the relevant monitoring period will be classified as having optimal adherence, whereas those with adherence below 80% will be classified as having suboptimal adherence [4,8,35].

For event-driven PrEP users, each PLP Camp check-in will capture sexual behavior and PrEP use occurring within the reporting interval, defined as the time since the previous check-in up to a maximum of 72 hours. Adherence will be assessed at the level of reported sexual encounters according to the standard 2-1-1 regimen. A reported sexual encounter will be classified as adherent if the participant reports taking 2 PrEP pills 2 to 24 hours before sex, 1 pill 24 hours after the initial dose, and 1 additional pill 48 hours after the initial dose. Event-driven users will be classified as having optimal adherence if all reported sexual encounters during the relevant monitoring period meet these dosing requirements; otherwise, they will be classified as having suboptimal adherence. Intervals without a submitted PLP Camp check-in will be treated as intervals without a reported sexual encounter, and therefore, event-level adherence will be assessed only for reported sexual encounters.

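### The primary outcome is defined as one 6-month status but analysed as a repeated measure, and no group contrast is identified as the primary test

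*Protocol article*

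**What the plan says.** The protocol article describes the primary outcome in two ways.

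- **One status per participant.** Abstract, Methods: "The primary outcome is the proportion of participants achieving optimal adherence for 6 months". Outcomes: "The primary outcome of this study is optimal PrEP adherence over the 6-month study period, defined as a binary outcome", and this is "assessed separately for event-driven and daily PrEP users". Sample Size Planning fits this description. For each regimen it compares two proportions once: 45% in control with a 17.5-point difference for event-driven users, and 60% with the same difference for daily users.
- **A repeated status.** Statistical Analysis: "The primary analysis will assess between-group differences in optimal PrEP adherence over time". On the choice of model it adds: "As the primary outcome is binary and repeatedly measured, generalized linear mixed-effects logistic regression models will be used". The model has terms for group, time and their interaction, with a random intercept for each participant. Results are to be given as odds ratios with 95% CIs. Missing Data Handling confirms that every available repeated adherence outcome enters this model.

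Outcomes also has wording that points to the second description. Daily users are classified by days with reported intake "out of all days under observation during each monitoring period". Event-driven users are optimal "if all reported sexual encounters during the relevant monitoring period meet these dosing requirements". Neither the length nor the number of these periods is given.

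**The concern.** One status over 6 months and a series of period-specific statuses are different variables. The difference is largest for event-driven users, because a single incorrect reported encounter makes the whole window suboptimal. The longer the window, the fewer participants qualify.

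A model with group, time and group-by-time terms also offers several answers to whether the intervention worked: the group effect at a given period, an effect averaged over periods, or the interaction. Under the usual reference-cell coding the group coefficient is the effect at the reference time only, and the interaction asks whether the effect changes over time. The article does not say which of these decides the trial. The trial is open label, so the choice should be on record before anyone sees the data.

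**Working it through.** **1. Reproduce the plan's figure (event-driven users).** Inputs from Sample Size Planning: control 0.45, intervention 0.45 + 0.175 = 0.625, power 0.80, 20% loss. From Statistical Analysis: two-sided 0.05.

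n per arm = [z(0.975)·√(2p̄q̄) + z(0.80)·√(p₁q₁ + p₂q₂)]² / d², with p̄ = 0.5375

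= (1.960 × 0.7051 + 0.8416 × 0.6942)² / 0.175² = 3.866 / 0.030625 = 126.2, so 127.

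127 / 0.80 = 158.75, so 159 per arm and 318 in total, against the stated 320. At 160 × 0.80 = 128 evaluable per arm, power is 80.5%. So 320 follows from one comparison of two proportions. (The printed Z of 1.64 would give 100 per arm and 250 in total. That mismatch is a separate point, as is the daily figure of 110, which this formula does not reproduce.)

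**2. Does the choice of contrast matter?** Simulation with 128 per arm and two-sided 0.05. Assumptions not in the documents: three follow-up periods, control rate 0.45 in each, latent within-person correlation 0.3 to 0.7, and Wald tests on proportions standing in for the mixed model.

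| Contrast | Constant 17.5-point effect | Effect growing to 17.5 points |
|---|---|---|
| Last period | 80-82% | 80-81% |
| Average over periods | 94-99% | 64-78% |
| Interaction, last minus first | about 5-6% | 32-46% |
| Interaction, joint test | about 5-6% | 24-37% |

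Under a constant effect there is no interaction to find, so its power is simply the significance level (simulated values 4.5% to 5.8%).

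**3. Do the two definitions give the same rate?** Take a random-intercept logistic model with 45% optimal in each period, and compute the chance of being optimal in every period.

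| Assumed ICC (logit scale) | All 3 periods | All 6 periods |
|---|---|---|
| 0.3 | 0.167 | 0.067 |
| 0.5 | 0.216 | 0.121 |
| 0.7 | 0.271 | 0.191 |

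The 45% used for event-driven users therefore cannot describe both a per-period and a whole-study status. With 62.5% per period in the intervention arm, the all-period rates are 0.333, 0.387 and 0.446 for three periods and 0.178, 0.257 and 0.347 for six. The gap between arms is then 0.166 to 0.175 for three periods and 0.111 to 0.156 for six. What clearly moves is the control rate. Whether the 17.5-point gap survives depends on the undefined number of periods.

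**4. Effect scale.** The planned effect is a marginal odds ratio of (0.625/0.375)/(0.45/0.55) = 2.04. The mixed model's odds ratio is conditional on the random intercept, roughly 2.04^√(1 + 0.346σ²): 2.28 at σ = 1, 3.00 at σ = 2 and 4.23 at σ = 3. Numerical integration gives slightly more: 2.36, 3.23 and 4.68. The documents give no σ.

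**The case against.** The best defence is that Outcomes, Statistical Analysis and Missing Data Handling can be read together as a per-period status followed for 6 months, with the abstract merely looser. An article may also leave the coding of time and the choice of coefficient to an analysis plan. Part of this stands: the monitoring-period wording softens the conflict, and a missing contrast alone would be a matter of detail. But a period without a length reconciles nothing, and an analysis plan faithful to the repeated-measures text would still conflict with the abstract and with the opening definition in Outcomes.

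Four stronger readings are tempting, and the documents do not support them.

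- A reader might infer an inflated false-positive rate from picking the best visit. No section lets success be claimed at any one of several visits. Months 1, 3 and 6 are survey visits, whereas the primary measure comes from the platform.
- A reader might infer that no available contrast was powered. A final-period comparison of 45% with 62.5% is what the event-driven calculation covers.
- A reader might call the conditional odds ratio wrong. It is a valid estimand, and how far it exceeds 2.04 depends on an unknown SD.
- A reader might object that the interaction cannot represent change from baseline. No section says that it will be read that way.

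**Conclusion.** The point holds in this form: the article gives two unreconciled definitions of its primary outcome and fixes a model with several candidate tests without naming the primary one. For the same constant 17.5-point effect, power runs from the significance level (interaction) to 94-99% (average), with 80-82% at the last period. For event-driven users, 45% per period corresponds to about 17-27% across three periods. These sizes rest on three assumed periods, the assumed correlations and a simplified test. The contradiction in the text does not depend on any of them. The odds-ratio scale is a reason to add a risk difference, not an error in itself.

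**What to change.** Before the data are viewed, state for each regimen one primary outcome variable with a defined monitoring period, and name one group contrast as the primary test.

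- **Simplest route.** Keep the mixed model and name the final-period (month 6) group contrast, which has the same form as the sample-size calculation. Report it as a model-standardized risk difference with 95% CI, with the odds ratio alongside. Make the group-by-time test and the other time points secondary.
- **If a single 6-month status is preferred.** Re-justify the 45% and 60% control rates for that definition, and say how participants observed for only part of the 6 months are classified.

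Either way, align the abstract, Outcomes and Statistical Analysis. The cost is wording only: the Results section says that the research team has not viewed the data. Naming the final period gives up the extra power that an average would have under a constant effect, but it performs better than the average if the effect builds up over time.

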### Missing Data Handling

Missing data are expected to arise primarily from incomplete or absent EMA check-ins and missed follow-up assessments. Prespecified regimen-specific rules used to derive adherence outcomes will be treated as part of the outcome definition rather than as missing data imputation. In the primary analysis, generalized linear mixed-effects models will use all available observed repeated adherence outcomes without requiring complete data at every follow-up time point. This likelihood-based approach allows participants with partially observed follow-up data to contribute to the analysis and is consistent with the intention-to-treat principle under the assumption that missingness depends on observed data.

Sensitivity analyses will be conducted to assess the robustness of the findings to alternative assumptions regarding missing data. First, multiple imputation by chained equations will be applied to missing interval-level adherence outcomes and missing covariate data. The imputation models will include study group, time, prior adherence, baseline characteristics, and other variables associated with adherence or missingness. Estimates from the imputed datasets will be combined using the Rubin rules. Second, complete-case analyses will be performed for comparison. Third, additional sensitivity analyses will examine less favorable assumptions for missing adherence outcomes to assess the extent to which the main conclusions depend on departures from the primary missing data assumption.

### Ethical Considerations

This study was approved by the institutional review board of Tsinghua University (THU01-20240097) on July 4, 2024 and was registered in the Chinese Clinical Trial Registry (ChiCTR2400088278) on August 14, 2024. Electronic consent will be obtained from all participants. Compensation will be provided after each survey completed in the form of electronic vouchers for the HeHealth store. The study findings will be reported in peer-reviewed publications and presented at relevant academic conferences.

## Results

Funding for the study was approved in March 2024. Ethics approval for the study was granted in July 2024. Recruitment and randomization commenced in November 2025. This included identification of eligible participants and randomization of the eligible participants to the control or intervention group until the required sample size was achieved. Baseline data collection commenced in January 2026. By February 5, 2026, recruitment and baseline data collection were completed, with 448 participants enrolled. The data have not been viewed by the research team. The intervention is expected to conclude in August 2026, and results are anticipated to be published in early 2027.

## Discussion

### Expected Findings

The REMOTE trial will evaluate the effectiveness of a digital intervention in improving the PrEP adherence of real-world users who purchase the medication online. The WeChat-based intervention platform incorporates a real-time monitoring function developed based on the EMA approach and precision intervention functions guided by the SCT. The ultimate goal of the REMOTE trial is to provide a feasible and effective tool to help e-consumers of PrEP keep optimal medication adherence to prevent HIV infection. The results of this study will have several important implications for future HIV prevention and broader public health interventions.

First, it addresses a critical gap in current PrEP adherence interventions by specifically focusing on online PrEP consumers, a growing population that faces unique barriers to optimal PrEP use [38,39]. By leveraging AI and EMA, the platform delivers personalized, context-specific interventions in real time, a feature that is crucial for addressing adherence challenges such as forgetting to take the medication or needing timely information and support [40]. Second, this intervention could serve as a model for integrating digital health platforms with real-world adherence monitoring, thereby improving outcomes in other health care areas that require long-term medication adherence (eg, antiretroviral therapy for HIV and chronic disease management) [31-43]. Additionally, the data collected through the intervention platform could offer valuable insights into user behavior and adherence patterns, contributing to future research on HIV prevention and personalized health interventions [44,45]. Policymakers and health care providers may leverage the study’s findings to enhance PrEP programs and expand the use of digital health platforms for preventive interventions, particularly among underserved populations. More importantly, the design and findings of this study may also inform similar efforts in other low- and middle-income countries or regions where online medication procurement is common, but adherence support remains limited. The model could be adapted to fit the sociocultural and infrastructural contexts of other settings, providing a feasible and effective framework for improving adherence to PrEP and other preventive medications delivered through digital channels.

### Strengths and Limitations

While this study offers a promising and innovative approach, several limitations should be acknowledged. First, participants will be conveniently recruited from PrEP clients of a single internet hospital, HeHealth, in China. Although HeHealth is currently the largest online platform for obtaining PrEP in China, the use of a single-platform sample may limit the generalizability of the findings to broader populations of PrEP users. Second, both PrEP adherence monitoring data and survey data will rely on self-report, which may be subject to social desirability bias and recall bias and, therefore, may lead to overestimation of adherence. Third, loss to follow-up may pose a challenge because of the online recruitment strategy and the relatively long follow-up period. Although a 10% to 20% attrition rate has been considered in the sample size calculation, higher-than-expected dropout could still reduce the statistical power of the study. Fourth, the effectiveness of the intervention may vary according to the level of participant engagement with the platform. Because the intervention depends on users actively interacting with its functions, such as behavior recording, health education materials, medication reminders, expert consultation, and the chatbot, low engagement may weaken its effect on adherence and warrants further investigation into factors that promote or hinder sustained use. In addition, as behavioral monitoring itself may influence medication adherence through self-awareness or self-tracking effects, this trial can only estimate the incremental effect of the precision intervention functions beyond the monitoring function rather than the effect of the full digital platform compared with usual care. Finally, this study is limited to oral PrEP and does not include all PrEP dosage forms. With the introduction of long-acting injectable PrEP, adherence challenges may differ across modalities. However, oral PrEP is expected to remain the predominant form of PrEP use in China for the foreseeable future, and therefore, this study is focused specifically on oral PrEP users.

## Data Availability

No datasets were generated or analyzed in this study, as this is a study protocol. Data to be collected in the future study will not be publicly available due to the sensitive nature of the information, but deidentified data will be available from the corresponding author on reasonable request, subject to ethical approval.

## Appendix

Multimedia Appendix 1 Baseline questionnaire.

Multimedia Appendix 2 Follow-up questionnaire.

Multimedia Appendix 3 Peer review report by Young Scientists Fund Project Review Committee, National Natural Science Foundation of China.

Multimedia Appendix 4 SPIRIT Checklist.

## Abbreviations

AI: artificial intelligence
EMA: ecological momentary assessment
PrEP: preexposure prophylaxis
REMOTE: Real-Time Monitoring and Precision Intervention for HIV Preexposure Prophylaxis Adherence
SCT: stages of change theory
SPIRIT: Standard Protocol Items: Recommendations for Interventional Trials
TTM: transtheoretical model
